#### Analysis of safety endpoint(s)

Safety analyses will be performed on the safety-evaluable population, defined as all subjects treated with at least one dose of investigational product.

In each cohort, toxicities and grades will be described according to the type of event at each cycle.

The global following data will also be given:
The number and percentage of patients with at least one adverse event over the study period,The number and percentage of patients with at least one grade 3 or 4 adverse event over the study period,The number and percentage of patients with at least one serious adverse event over the study period,The number and percentage of patients with at least one adverse event leading to treatment premature stop over the study period.

In case a patient experience more than one toxicity, the toxicity with the highest grade will be considered.

Time until grade 3–4 toxicity will be determined using the Kaplan Meier method. Patients without toxicities will be censored.

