### Study endpoints

The primary endpoint is progression free survival (PFS) 6 months after the initiation of immunotherapy for all cohorts, with the exception of ovarian cohort evaluated at 12 months. PFS is defined as the time from the date of first dose of immunotherapy to the date of progression or death from any cause. Progression will be defined using iRECIST criteria.

Secondary endpoints are:
Disease control rate, including stable and responsive disease, evaluated 6 months after immunotherapy initiation for all cohorts except ovarian cohort, evaluated at 12 months.Overall survival (OS) evaluated at 12 and 24 months after immunotherapy initiation defined by the time of the first immunotherapy dose to the date of death from any cause.Response rate evaluated by CT scan, RECIST evaluation after 6 weeks of olaparib therapy.Olaparib toxicity evaluated at the end of STEP1 using CTCAE V5.Olaparib + immunotherapy (tremelimumab + durvalumab) toxicity evaluated at 3, 6 and 12 months after immunotherapy initiation using CTCAE V5.

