### Investigational products

Olaparib, durvalumab and tremelimumab will be supplied by AstraZeneca.

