#### Sample size calculation

Sample size was determined using an A’Hern’s single stage design. The primary endpoint is progression PFS. It will be evaluated at 6 months (except for ovarian cancer with an evaluation at 18 months given the results of olaparib in SOLO-2 trial). The hypotheses are the following:
one-sided alpha risk =10%, a power = 90%,the expected rate of patients stable or in response after 6 weeks of olaparib is 80%,the expected rate of patients non-evaluable the primary endpoint is 5%,P0 and P1 are determined using hypotheses detailed above.

P0 is the highest level of inefficacy for which the new treatment will be rejected (maximal inefficacity). P1 defines the minimum required level of efficacy. The design of the trial focuses on demonstrating that this level is plausible given that the trial results and the efficacy is greater than the first proportion, P0. Taking into account these hypotheses: 270 patients will be included in the study, and at least 213 are required for statistical analyses. At the end the study, analysis of the primary endpoint will be performed on evaluable patients who were in response or stable after 8 weeks of olaparib.

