#### Interim analyses

An Independent Data Monitoring Committee (IDMC) will be established for Guid2Repair trial. The IDMC will consist of designated sponsor, 2 or 3 experts in oncology and 1 statistician. The IDMC will be responsible for an independent evaluation of the safety for the patients participating in the clinical trial. Additional IDMC meetings could be required if more than 15% of ongoing patients have experienced an adverse event ≥ grade 3.

No interim analyses are planned for efficacy.

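### One safety set for both steps, a grade 3–4 limit that omits fatal events, and an IDMC percentage on ongoing patients blur the combination's severe-toxicity rate

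*Protocol article*

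**What the plan says.** All references are to the protocol article.

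- **Safety set.** Analysis of safety endpoint(s) uses one population: "Safety analyses will be performed on the safety-evaluable population, defined as all subjects treated with at least one dose of investigational product". The Investigational products section covers all three drugs: "Olaparib, durvalumab and tremelimumab will be supplied by AstraZeneca". Under Study procedures, a patient who progresses on the STEP 1 scan leaves the study and so never receives durvalumab or tremelimumab.
- **Numbers.** Sample size calculation: "270 patients will be included in the study, and at least 213 are required for statistical analyses". Study population and eligibility criteria gives 213 as the number expected to enter STEP 2.
- **Severe events.** Among the global summaries is "The number and percentage of patients with at least one grade 3 or 4 adverse event over the study period". Time to toxicity is also restricted to grades 3–4, is estimated by Kaplan-Meier, and carries the rule "Patients without toxicities will be censored". A patient with several toxicities is counted at the worst grade.
- **Monitoring.** Interim analyses: "Additional IDMC meetings could be required if more than 15% of ongoing patients have experienced an adverse event ≥ grade 3".
- **Text that separates the steps.** Study endpoints lists olaparib toxicity at the end of STEP 1 as its own endpoint, and then "Olaparib + immunotherapy (tremelimumab + durvalumab) toxicity evaluated at 3, 6 and 12 months after immunotherapy initiation using CTCAE V5". The safety section also plans tables by cycle within each cohort.

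**The concern.** The combination's toxicity is a question in its own right. It has its own secondary endpoint, and the Abstract names safety alongside efficacy in the primary endpoint. The efficacy section restricts its population to patients who received at least one dose of durvalumab plus tremelimumab. The safety section has no counterpart, so its headline percentages average two different exposures: a few weeks of olaparib alone, and olaparib followed by dual immunotherapy.

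Two further rules affect the most serious events. Limiting the severe-event figures to grades 3–4 leaves no place for a toxicity that is fatal outright. And the only numerical safety trigger in the article is a share of ongoing patients, although Table 3 takes patients with certain severe events off treatment. At stake is whether the severe-toxicity rate in the report, and the rate that prompts an extra IDMC meeting, are the rates a reader would take them to be.

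**Working it through.** **1. Size of the olaparib-only group.** The inputs are 270 included, 213 expected in STEP 2, and 80% expected to be stable or responding after STEP 1 (Sample size calculation). First, the plan's own figure: 213 / 0.80 = 266.25, rounded up to 267, against 270; and 270 × 0.80 = 216, against 213. The STEP 2 count therefore reproduces closely. (Adding the 5% non-evaluable allowance gives 270 × 0.80 × 0.95 = 205, so 213 fits as a count of STEP 2 entrants and not as a count of evaluable patients. That is a separate matter.) Olaparib-only patients: 270 − 213 = 57, and 57 / 270 = 21.1%; from the 80% assumption, 54 / 270 = 20%.

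**2. Effect on the whole-study percentages.** Let p_c be the share of STEP 2 patients with the event and p_o the share of olaparib-only patients with it.

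Reported rate = (213 × p_c + 57 × p_o) / 270 = 0.789 p_c + 0.211 p_o

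The article gives neither rate, so both are assumed. Example: (213 × 0.40 + 57 × 0.10) / 270 = 90.9 / 270 = 33.7%.

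| Assumed p_c | p_o = 0 | p_o = 10% | p_o = 20% |
|---|---|---|---|
| 40% | 31.6% | 33.7% | 35.8% |
| 50% | 39.4% | 41.6% | 43.7% |

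The relative shortfall is at most 21% (p_o = 0) and vanishes when p_o = p_c. These are all-cohort figures. Attrition, and so dilution, may differ by cohort, and the article gives no cohort sizes.

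**3. Grade 5.** Set side by side, the safety section counts and times grades 3–4, while Interim analyses uses grade 3 and above. Under the first, a patient whose only severe event is fatal meets neither the count nor the time-to-event definition. The worst-grade rule adds an ambiguity: a patient who goes from grade 3 to grade 5 is classed as grade 5 and could also fall out. If 1%, 2% or 5% of the 213 STEP 2 patients (assumed) had a fatal toxicity as their only severe event, 213 × 0.01 = 2.1, 213 × 0.02 = 4.3 and 213 × 0.05 = 10.7, so about 2, 4 or 11 patients would be missing.

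**4. IDMC percentage.** Take 100 treated patients (assumed), 40 stopped and 60 ongoing.

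- Stopped 40% affected (16 patients), ongoing 10% (6): the rule reads 6 / 60 = 10% and is not met; among all treated the rate is 22 / 100 = 22%.
- Stopped 10% affected (4), ongoing 16% (9.6 on average): the rule reads 16% and is met; among all treated the rate is 13.6 / 100 = 13.6%.
- Stopping unrelated to toxicity, with a true rate of 20% and half of each group stopped: 0.10 / (0.10 + 0.40) = 20%, so no distortion.

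The figure depends on who has stopped, and the error can go either way.

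**5. Time to toxicity.** The article makes no provision for death without prior severe toxicity. If such deaths are censored, one minus the Kaplan-Meier estimate lies at or above the cumulative incidence, because a patient who has died can no longer have the event. The gap depends on toxicity and death rates that the article does not give.

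**The case against.** The strongest reply is that the article already separates the steps where it matters. The endpoint for the combination is timed from the start of immunotherapy, a time point that an olaparib-only patient does not have; STEP 1 toxicity is a separate endpoint; and the by-cycle tables show which treatment was being given. An overall table of everyone treated is legitimate. Fatal events still appear in the any-event and serious-event counts and in the description of grades. The IDMC rule only says that extra meetings might be needed; it is not a stopping rule. The rest is wording that an analysis plan or IDMC charter could settle.

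Much of this stands, and it rules out four stronger readings that a reader might infer:

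- *Every combination rate will be divided by 270, so a true 40% becomes 32%.* No section says so. A multiplier of about 0.8 is only the limiting case for the whole-study percentages, when olaparib-only patients have no events.
- *A patient with a fatal toxicity will be censored as free of toxicity.* The text censors patients without toxicities, and this patient is not one. The article leaves the case unassigned.
- *The trigger always understates.* The second example in the working shows the opposite, and the article does not define ongoing.
- *The Kaplan-Meier curve greatly overstates toxicity because progression is a competing event.* Follow-up continues after treatment ends, and the retreatment section allows some treatment beyond progression, so progression need not end observation. Any figure would rest on assumed hazards.

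What does not stand is the claim that these are mere omissions. The article states the population, the grades and the basis of the trigger; followed as written, they give the results above.

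**Conclusion.** The point holds in a limited form. The share of olaparib-only patients in the safety set, 57 of 270 (21%), follows from the article's own counts. The resulting dilution applies to the global whole-study percentages, and to any STEP 2 rate computed on that single set; its size needs assumed rates and ranges from nothing to a 21% relative understatement when olaparib-only patients have the lower rate. The conflict between grades 3–4 and grade 3 or higher is in the text and needs no assumption; only the number of patients affected does. The IDMC percentage, on the plain meaning of ongoing, is not the rate among all treated and can miss it in either direction. For time to toxicity, the direction is clear for deaths that are censored, but the size cannot be derived from the article. The analyses concerned are descriptive and the efficacy design is untouched. The changes are worth making because they concern the headline severe-toxicity figures and the only numerical safety trigger, at almost no cost.

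**What to change.** 1. Report safety separately for STEP 1 (at least one olaparib dose, events before immunotherapy) and STEP 2 (at least one dose of durvalumab or tremelimumab, events from that dose). Keep the overall table.
2. In the safety section, replace both grade 3–4 limits with grade 3 or higher, including grade 5, to agree with Interim analyses.
3. Compute the IDMC percentage among all patients who started the step, whether or not they are still on treatment.
4. Present time to first grade 3 or higher toxicity as cumulative incidence, with death without prior such toxicity as a competing event. Add progression as a competing event only if adverse event collection ends there, and state whether it does.

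The cost is revised wording and a few extra tables.

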### Study objectives

The primary objective of the study is to evaluate the efficacy of olaparib + immunotherapy (durvalumab + tremelimumab) during 4 months, followed by durvalumab alone as maintenance treatment in patients with solid cancers and in response or stable, after prior molecular target therapy by olaparib based on molecular sequencing (mutation in homologous gene repair).

Study secondary objectives are:
To evaluate 6-month disease control rate (DCR) for all cohorts, except ovarian cohort which will be evaluated at 12-months.To evaluate 1 and 2-year PFS and overall survival (OS).To evaluate response rate after 6 weeks of olaparib therapy (STEP 1).To evaluate safety of molecular therapy by olaparib at the end of STEP1.To evaluate safety of molecular therapy (olaparib) + immunotherapy (durvalumab + tremelimumab) and immunotherapy in maintenance (durvalumab alone).

The study exploratory objective is to evaluate the immunogenic effect of olaparib (modification of immune infiltrate and immunogenic cell death markers on biopsy performed before and after olaparib treatment).

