### Study procedures

All patients respecting all eligibility criteria, namely presenting mutations in homologous repair genes will be included. Regimens sequence is presented in Fig. 1. Study will be divided into two successive steps:
*Step 1*After 6-weeks of olaparib, all patients from STEP 1 will have a CT scan.*Step 2*Depending on CT scan results, two situations will occur:
Patients with stable disease or partial response will follow olaparib + immunotherapy by durvalumab + tremelimumab during 4 months and then continue with durvalumab alone until progression or until 24 dosing maximum of durvalumab for all cohorts except for ovarian cohort with a maximum of 36 dosing.Patient with progression will be withdrawn from the study and treated according to standard care.

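### The four overall safety percentages pool the olaparib-alone and combination periods in one any-dose population, so they estimate neither of the two safety endpoints the protocol sets

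*Protocol article*

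**What the plan says.** The section on analysis of safety endpoints in the protocol article defines the population in one sentence: "Safety analyses will be performed on the safety-evaluable population, defined as all subjects treated with at least one dose of investigational product". No other safety population is named. Olaparib counts as an investigational product: "Olaparib, durvalumab and tremelimumab will be supplied by AstraZeneca" stands under that heading.

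The section then plans three kinds of output:

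- A description by cohort and cycle: "In each cohort, toxicities and grades will be described according to the type of event at each cycle".
- Four global summaries (any adverse event, grade 3 or 4, serious, and leading to early treatment stop), all with the same window. For example: "The number and percentage of patients with at least one grade 3 or 4 adverse event over the study period".
- A Kaplan-Meier analysis of time to grade 3-4 toxicity, with censoring of patients without toxicity and no stated time origin.

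The objectives and endpoints treat the two steps as separate safety questions. For STEP 1 the endpoint is "Olaparib toxicity evaluated at the end of STEP1 using CTCAE V5". For STEP 2 the objective begins "To evaluate safety of molecular therapy (olaparib) + immunotherapy (durvalumab + tremelimumab) and immunotherapy in maintenance (durvalumab alone", and the matching endpoint is assessed at 3, 6 and 12 months counted from the start of immunotherapy.

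Not everyone reaches STEP 2. Under study procedures, "Patient with progression will be withdrawn from the study and treated according to standard care". The sample size section assumes that "the expected rate of patients stable or in response after 6 weeks of olaparib is 80" per cent.

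**The concern.** The stated population and window do not fit the stated endpoints. A patient who takes olaparib, progresses at the STEP 1 scan and leaves is in the safety set but was never at risk of a durvalumab or tremelimumab reaction. A patient who continues contributes to the same count whether the severe event came on olaparib alone or on the three drugs together. The four global percentages therefore mix two exposures and two groups of patients.

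At stake is the secondary objective on the safety of the combination, for which the article names no exposed denominator. The efficacy section handles the same issue differently: its modified intention-to-treat set requires at least one dose of durvalumab plus tremelimumab.

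**Working it through.** **Inputs.** Included: 270 (sample size section). Expected in STEP 2: 213 (study population section). Share stable or responding after olaparib: 80%. Share not evaluable for the primary endpoint: 5% (both sample size section). I assume that every included patient takes at least one olaparib dose and that the 213 all receive immunotherapy. The article gives no adverse event rates, so all rates below are assumptions.

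**Reproducing the plan's figure.** 270 × 0.80 = 216, against the stated 213, a difference of under 2%. Applying the 5% as well gives 270 × 0.80 × 0.95 = 205, which does not match. So 213 is best read as the number entering STEP 2, and I use 213 and 216 as the range.

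**Unexposed share of the safety set.** (270 − 213)/270 = 57/270 = 21.1%. At exactly 80%: (270 − 216)/270 = 54/270 = 20.0%.

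**Dilution of an event confined to STEP 2.** If such an event were divided by the whole safety set, the displayed rate would be the true rate times 213/270 = 0.789 (or 216/270 = 0.80):

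| Assumed rate among exposed | Shown over 270 (213 exposed) | Shown over 270 (216 exposed) |
|---|---|---|
| 20% | 15.8% | 16.0% |
| 40% | 31.6% | 32.0% |
| 60% | 47.3% | 48.0% |

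**Pooling over the whole study.** Let q be the chance of a grade 3-4 event in STEP 1 and p the chance in STEP 2, assumed independent, with q equal in those who do and do not continue. The whole-study percentage is

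[213 × (1 − (1 − p)(1 − q)) + 57 × q] / 270.

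For p = 40% and q = 20%: [213 × 0.52 + 57 × 0.20]/270 = (110.76 + 11.40)/270 = 45.2%. This is not the olaparib rate (20%), the combination rate (40%) or the cumulative rate in patients who had both steps (52%).

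**Direction.** With p held at 40%:

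| q | Whole-study figure | Against p = 40% |
|---|---|---|
| 10% | (213 × 0.46 + 5.7)/270 = 38.4% | below |
| 20% | 45.2% | above |
| 30% | (213 × 0.58 + 17.1)/270 = 52.1% | above |

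With f = 213/270, the pooled figure equals q + f·p·(1 − q). Setting it equal to p gives q = p(1 − f)/(1 − f·p) = 0.4 × 0.2111/(1 − 0.3156) = 12.3%. Below that STEP 1 rate the pooled figure understates the combination rate; above it, it overstates it.

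**The case against.** The strongest reply is that the article already separates the steps in time. Toxicity is described at each cycle. The dosing section allows up to four combination cycles and labels the first durvalumab-alone dose as cycle 5, so combination and maintenance can be told apart. The endpoints section fixes separate time points for each step, and a patient who never started immunotherapy has no 3-month point after starting it. An any-dose safety set is a conventional outer population, and an unseen full protocol or SAP may define step-specific sets within it. The body of the article makes safety secondary, and no decision rule depends on these percentages.

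Much of this stands. A reader might infer that every safety percentage is diluted, that STEP 1 and STEP 2 toxicity cannot be distinguished, or that the combination will look safer than it is. The article does not support those readings. The whole-study window applies only to the four global summaries. Nowhere does the article say that combination-specific counts will be divided by all treated patients, so the 0.79 to 0.80 factor is conditional on that choice. As the working shows, the pooled figure can err in either direction.

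The reply does not rescue the four global summaries, which pool both steps by their own wording. Nor is this merely detail left to another document: the article does fix a population and a window, and they do not match its endpoints. For the by-cycle and time-point outputs, the only population stated is still the any-dose set.

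**Conclusion.** The point holds for the four global percentages. They combine olaparib-alone and combination events and include about 57 of 270 patients (21%; 54 at exactly 80%) expected never to receive immunotherapy, so they estimate neither the olaparib rate nor the combination rate. The direction of the error cannot be stated in advance. Two smaller gaps go with it: no exposed denominator is given for the outputs that do separate the steps, and time to grade 3-4 toxicity has no start date. If that time runs from first olaparib, it mixes the six weeks of monotherapy with combination time.

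The 21% rests on the plan's own expected numbers and is an average over all cohorts. Since each cohort is analysed separately, the share will vary between cohorts. The event-rate examples illustrate size only. This is a cheap improvement to descriptive secondary analyses and does not touch the primary efficacy result.

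**What to change.** Replace the single definition with two safety sets:

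- **STEP 1 set:** patients with at least one olaparib dose, counting events from that dose until just before the first immunotherapy dose.
- **STEP 2 set:** patients with at least one dose of durvalumab or tremelimumab, counting events from that dose on.

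Report the four percentages and the time to grade 3-4 toxicity for each set, by cohort, with time starting at that set's first dose. Use the STEP 2 set as the denominator for the 3-, 6- and 12-month toxicity endpoint. Keep the all-treated, whole-study figures as a labelled overview.

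No new data, patients or visits are needed. The cost is a change of wording and one more set of tables, and the combination rates may turn out less favourable than the pooled ones.

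### The severe-toxicity count and the time-to-toxicity analysis stop at grade 4, so a patient whose only severe toxicity is fatal is missed by both

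*Protocol article*

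**What the plan says.** Under *Study endpoints* in the Protocol article, toxicity of the combination is "toxicity evaluated at 3, 6 and 12 months after immunotherapy initiation using CTCAE V5"; toxicity of olaparib alone is graded on the same scale at the end of STEP 1.

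Under *Analysis of safety endpoint(s)*, in the population with at least one dose, the article fixes:

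- the severe-toxicity count: "The number and percentage of patients with at least one grade 3 or 4 adverse event over the study period";
- the time-to-event analysis: "Time until grade 3–4 toxicity will be determined using the Kaplan Meier method", followed by the only censoring rule given, "Patients without toxicities will be censored";
- the rule for several toxicities in one patient: "In case a patient experience more than one toxicity, the toxicity with the highest grade will be considered".

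The same section plans summaries with no upper grade limit: "In each cohort, toxicities and grades will be described according to the type of event at each cycle", a count of patients with any adverse event, and "The number and percentage of patients with at least one serious adverse event over the study period".

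Under *Interim analyses*, additional IDMC meetings may be called if "more than 15% of ongoing patients have experienced an adverse event ≥ grade 3".

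**The concern.** CTCAE has a grade above 4: grade 5 is death related to the event. Both severe-toxicity summaries are written as closed ranges that end at 4, whereas the IDMC trigger is open at the top. The narrower definition is stated twice, so this is a fixed rule and not a detail left open. An analysis plan that follows the protocol faithfully would carry it forward.

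The direction of any error is known. Leaving out a fatal toxicity can only lower the reported severe-toxicity percentage and remove a downward step from the curve of freedom from severe toxicity. The study is non-randomized, so the absolute rates are what readers will use to judge the tolerability of olaparib with durvalumab and tremelimumab, and no control arm shares the same omission.

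**Working it through.** **No stated figure to reproduce.** The article gives no expected toxicity rate, safety threshold or safety sample size. The check is therefore of the definitions, followed by an illustration on assumed rates.

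**Step 1. Apply the definitions to four kinds of patient.**

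| Patient | Severe-toxicity count | Time to toxicity |
|---|---|---|
| Grade 3 or 4 event only | Counted | Event |
| Separate grade 3 or 4 event, later a fatal one | Counted on the words of the count; lost if the highest-grade rule is applied to it | Event at the earlier toxicity |
| One toxicity that worsens from grade 3–4 to grade 5 | Lost if classed by its highest grade | Unclear: depends on whether the earlier grade is used |
| Only severe toxicity is fatal | Not counted | Not a grade 3–4 event; no rule says how it is handled |

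The last row follows from the text with no further interpretation. The second and third depend on how the highest-grade sentence is applied, which the section does not say.

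**Step 2. Size of the effect on the count.** Inputs:

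- N = 270 patients to be included (*Sample size calculation*), taken as the safety population.
- f = proportion of patients with a fatal adverse event. Not in the document; assumed 1% to 3%.
- s = share of those patients not otherwise counted as grade 3 or 4. Not in the document; full range 0 to 1.

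Understatement = f × s; patients missed = N × f × s.

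| f | s = 0 | s = 0.5 | s = 1 |
|---|---|---|---|
| 1% | 0 | 0.5 points (1.4 patients) | 1 point (2.7 patients) |
| 2% | 0 | 1 point (2.7 patients) | 2 points (5.4 patients) |
| 3% | 0 | 1.5 points (4 patients) | 3 points (8.1 patients) |

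The range is 0 to 3 percentage points, or 0 to about 8 of 270 patients.

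**Step 3. Size of the effect on the 12-month Kaplan-Meier estimate.** Assume constant hazards, with g the 12-month probability of a grade 3–4 toxicity (assumed 30% or 50%) and f as above for a fatal one:

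- λg = −ln(1 − g)/12 and λf = −ln(1 − f)/12.
- Fatal toxicity not an event: 1 − exp(−12λg) = g.
- Fatal toxicity an event: 1 − exp(−12(λg + λf)) = 1 − (1 − g)(1 − f).
- Difference: f × (1 − g).

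For g = 30% the difference is 0.7, 1.4 and 2.1 points at f = 1%, 2% and 3%. For g = 50% it is 0.5, 1.0 and 1.5 points. The range is about 0.5 to 2.1 points.

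**Step 4. Is the case likely to arise?** The chance of at least one fatal adverse event among 270 patients is 1 − (1 − f)^270: 74% at f = 0.5% and 93% at f = 1%. This is the chance of a fatal event, not of one that goes uncounted.

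**The case against.** The strongest reply is that little is lost and nothing depends on it. Most of that stands.

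- **Fatal events do not disappear.** A reader might infer that they would surface only among the serious adverse events. The section does not support this: the per-cohort description by type of event has no grade limit, and the any-event count includes them too.
- **The highest-grade rule need not remove anyone from the count.** A patient with a separate grade 3 or 4 event and a later fatal one still has at least one grade 3 or 4 event. The highest-grade sentence does not say that it overrides the count, so this loss is possible, not fixed.
- **The censoring of a fatal toxicity is not written down.** The rule censors patients without toxicities, and a patient who died of one is hardly that. The text is unclear; it does not direct that such patients be censored as toxicity-free.
- **A fatal toxicity does not improve the curve.** Censoring never raises a Kaplan-Meier estimate. The curve only fails to step down where it should.
- **The upper end of the range is not the expected result.** It requires that no patient with a fatal event is otherwise counted. Nor can a per-cohort effect be derived, since cohort sizes are not given.
- **The IDMC trigger is a different statistic.** It uses ongoing patients, and only says that extra meetings could be required. It shows that the article uses an open-ended threshold elsewhere; it is not a second definition of the same rate.
- **No threshold, sample size or decision rule uses the grade 3–4 count**, and the article does not name it as a headline result.

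What the reply does not remove is the patient whose only severe toxicity is fatal. On the words as written, that patient is absent from both severe-toxicity summaries.

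**Conclusion.** The wording is wrong as written, and the consequence is minor. Two summaries meant to describe severe toxicity exclude its most severe grade, while the monitoring threshold in the same article does not. The defect is confined to those two summaries.

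Its size rests on assumptions, because the article gives neither a fatal-event rate nor the overlap with other severe events. At a fatal-event rate of 1–3%, the count is understated by 0 to 3 percentage points; under the constant-hazard illustration, the 12-month Kaplan-Meier estimate is understated by about 0.5 to 2.1 points. The effect is on reporting, not on any decision in the trial.

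**What to change.** Under *Analysis of safety endpoint(s)*, define both the severe-toxicity count and the time-to-toxicity analysis on grade 3 or higher (grades 3–5), in line with the threshold under *Interim analyses*. State that a fatal toxicity counts as an event in the time-to-toxicity analysis. With the open-ended definition, the highest-grade rule can no longer move a patient out of the count, so that ambiguity is settled too.

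The cost is a few words. Sample size, conduct and treatment are unaffected. The one downside is that the reported severe-toxicity rate may rise slightly.
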